### Participant timeline {13}

Applicants register on an encrypted study platform that uses a two-step authentication where information about the study and the informed consent form can be found. Prospectively eligible applicants will undergo a thorough assessment of eligibility using the MINI, CAPS-5, and a structured suicide risk evaluation assessment. Eligible participants will be invited to participate in the study if the inclusion criteria are met, as stated in Table 1.

### Sample size {14}

A power calculation was conducted to determine the number of participants needed to evaluate intensive treatment compared to weekly delivered sessions. The power analysis for the trial is based on the CAPS-5, where a significant difference in treatment effects between groups would be set to at least 10 points. With an estimated standard deviation of the CAPS-5 of 20, this represents a standardized mean difference in terms of Cohen’s *d* of 0.5 [24]. Given 95% power, 10% data attrition rate, and an alpha level of 0.05, we estimate that we would need a total of 140 participants to find a statistically significant moderate between-group effect of *d* = 0.5 at our primary endpoint (1 month). We also conducted a power analysis to ensure that we would be able to detect our expected differences in dropout rate, a reduction in the dropout rate from a 22% baseline rate to 5% in the intervention group with conditional linear regression, conditional on the four randomization strata arising from the combination of sex (male, female) and trauma onset (childhood, adulthood). The power was estimated with 1000 randomly generated datasets. The following table shows the estimated power with different sample sizes (*n*).

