### Intervention description {11a}

#### Intensive treatment (iPE)

The intensive treatment adheres to the original treatment protocol for prolonged exposure [10] with three major exceptions. First, treatment is delivered for five consecutive days followed by three 60-min individual booster sessions dispersed 1, 2, and 4 weeks afterwards. Second, treatment combines individual and group formats. Each patient will receive nine individual sessions focused on confronting the memory of the traumatic event (imaginal exposure and processing) and five group sessions with psychoeducation, breathing retraining, overall rationales, and preparing work with confronting trauma-related situations in the patient’s daily life (in vivo exposure). Starting from day 2, the group sessions shift their focus to the formulation of individually tailored designed exercises for individual implementation during these sessions. Third, there is no assigned homework between treatment days; instead, time is allocated between daily sessions for working on exposure exercises.

The treatment will be delivered for an average of 7 h of treatment each day for five consecutive days. Three individual 60-min booster sessions will be conducted, which will include imaginal exposure, follow-up on in vivo exposure exercises, a comprehensive summary of the treatment and lessons learned, as well as discussions on relapse prevention and planning for continued self-practice. These booster sessions will be dispersed 1, 2, and 4 weeks after the intensive treatment week. The total treatment period is 5 weeks, which encompasses the intensive treatment and booster sessions.

Table 2 shows a typical treatment schedule for the iPE week.

**Table 2 Tab2:** A typical treatment schedule for the iPE week

Monday	Tuesday	Wednesday	Thursday	Friday
**INTRO MEETING** 9:00 – 9:30	**IMAGINAL EXPOSURE SESSION 2** 8:30 – 9:30	**IMAGINAL EXPOSURE SESSION 4** 8:30 – 9:30	**IMAGINAL EXPOSURE SESSION 6** 8:30 – 9:30	**IMAGINAL EXPOSURE SESSION 8** 8:30 – 9:30
**GROUP SESSION 1 PSYCHOEDUCATION, OVERALL RATIONALE, PREPARATION IN VIVO** 9:30 – 11:00	Break 9:30 – 10:00	Break 9:30 – 10:00	Break 9:30 – 10:00	Break 9:30 – 10:00
	**OWN WORK** 10:00 – 11:00	**OWN WORK** 10:00 – 11:00	**OWN WORK** 10:00 – 11:00	**OWN WORK** 10:00 – 11:00
**LUNCH** 11:00 – 12:00	**LUNCH** 11:00 – 12:00	**LUNCH** 11:00 – 12:00	**LUNCH** 11:00 – 12:00	**LUNCH** 11:00 – 12:00

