## Discussion

The study is the first trial to directly compare an intensive treatment for PTSD with first-line individual PE delivered for 15 weekly sessions in a Swedish psychiatric setting. The study is well powered as a superiority trial. If iPE are superior or comparable in terms of clinical efficacy and come with a lower dropout rate as well as faster recovery, it should be considered a candidate for implementation in regular care.

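### The stated 95% power for d = 0.5 does not follow from 140 participants and 10% attrition; those inputs give about 80%

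*Protocol article*

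**What the plan says.** Sample size {14} bases the calculation on the CAPS-5 at the 1-month primary endpoint. It fixes the target as follows: "a significant difference in treatment effects between groups would be set to at least 10 points". It then gives the spread, "With an estimated standard deviation of the CAPS-5 of 20", and converts the two into Cohen's d = 0.5. The result is stated in one sentence: "Given 95% power, 10% data attrition rate, and an alpha level of 0.05, we estimate that we would need a total of 140 participants". Whether alpha is one- or two-sided is not said. No baseline correlation, covariate adjustment or repeated-measures gain is mentioned. Sequence generation {16a} sets 1:1 allocation.

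Two other places bear on the point. The Discussion concludes: "The study is well powered as a superiority trial". The description of the intensive arm says: "Second, treatment combines individual and group formats". That arm has five group sessions alongside the individual ones, and the sample-size paragraph mentions no allowance for them.

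**The concern.** The paragraph prints every input of a standard two-group calculation together with its answer, so the answer can be checked directly. A total of 140 is familiar as the size for d = 0.5 at 80% power with 10% attrition. Power of 95% normally needs far more.

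This is the power statement for the primary endpoint. If true power is near 80%, the risk of missing a real 10-point benefit is about 20% rather than 5%. The Discussion says that iPE should be considered for routine care if it is superior or comparable. A non-significant result, read alongside a claimed 95% power, could be taken as stronger evidence against a 10-point benefit than the design can give.

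**Working it through.** **Inputs.** From Sample size {14}: difference 10, SD 20, so d = 10/20 = 0.5; alpha 0.05; attrition 10%; N = 140; stated power 95%. From Sequence generation {16a}: 1:1 allocation. Analysed: 140 × 0.9 = 126, or 63 per arm. Two-sided testing is assumed first because sidedness is not given.

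**Step 1: the plan's own figure.** Per arm, n = 2(z₁₋α/₂ + z_power)²/d².

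- For 95% power: 2(1.960 + 1.645)²/0.25 = 103.96, so 104 per arm, 208 analysed, and 208/0.9 = 232 randomised. The noncentral t version gives 104.9 per arm, so 210 analysed and 234 randomised.
- For 80% power: 2(1.960 + 0.842)²/0.25 = 62.8, so 63 per arm, 126 analysed, and 126/0.9 = 140 exactly.

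The printed N = 140 is reproduced by 80% power and not by 95%.

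**Step 2: power at the planned size.** Power ≈ Φ(d√(n/2) − z₁₋α/₂). With n = 63, 0.5 × √31.5 = 2.806, and Φ(2.806 − 1.960) = Φ(0.846) = 0.801.

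| Reading | Analysed per arm | Normal | Noncentral t |
|---|---|---|---|
| Two-sided, 10% attrition | 63 | 0.801 | 0.795 |
| Two-sided, no attrition | 70 | 0.841 | 0.836 |
| One-sided, 10% attrition | 63 | 0.877 | 0.874 |
| One-sided, no attrition | 70 | 0.905 | 0.903 |

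None reaches 0.95. One-sided testing at 95% power would still need 194 to 196 randomised.

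**Step 3: what 63 per arm detects with 95% power.** d = (1.960 + 1.645) × √(2/63) = 0.642 (noncentral t: 0.647). At SD 20 that is 12.8 to 12.9 CAPS-5 points.

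**Step 4: could an unstated analysis supply 95%?**

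- Covariance adjustment multiplies the variance by 1 − r². Then 104.9(1 − r²) = 63 gives r = √(1 − 63/104.9) = 0.63.
- A change score has variance 2(1 − r) times the raw variance. Then 103.96 × 2(1 − r) = 63 gives r = 0.70.
- At r = 0.5, covariance adjustment gives two-sided power of 0.90.

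**Step 5: sensitivity, on conditions the plan does not state.**

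- If outcome data were lost at the 22% and 5% used in the separate dropout calculation, the arms would have 70 × 0.78 = 54.6 and 70 × 0.95 = 66.5 analysed. Power would be about 0.775 (noncentral t).
- For clustering in iPE groups, multiply the variance of the iPE mean by 1 + (m − 1) × ICC. Assumed ranges, not in the document, are m = 4 to 8 and ICC = 0.02 to 0.10. The factor runs from 1.06 to 1.70, and power from 0.79 down to 0.68 (normal approximation).

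**The case against.** The strongest defence is that the article names no analysis model. The abstract defines the primary outcome as change on the CAPS-5, the scale is measured at enrolment, and baseline adjustment is ordinary practice. With a correlation of about 0.63 the same 140 would give 95%. It follows that the power of the eventual analysis may exceed 80%. The printed sentence remains wrong, because it derives 140 from the listed inputs alone and standardises by the raw SD of 20. A separate analysis plan cannot make that derivation correct.

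The secondary figures deserve caution. The 22% and 5% are treatment dropout rates, and participants who stop treatment are encouraged to complete all assessments, so 0.775 is a what-if value and not a forecast. The clustering range rests on assumed group sizes and ICCs, most iPE sessions are individual, and how clustering is analysed may be covered in the plan on OSF. The central error depends on neither.

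It can also be said that 80% is a conventional planning level, and that the confidence interval, not the planned power, will show whether a 10-point benefit is excluded. Both are true. They bear on how much harm follows, not on whether the figure is right. The simulated power table (0.878 at n = 140) concerns dropout rates and lends the 95% no support.

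**Conclusion.** The concern holds. On the stated inputs, two-sided power for a 10-point difference is 0.795 to 0.80, about 15 percentage points below the stated 0.95. The type II error is about 20% instead of 5%. The exact match 126/0.9 = 140 suggests that 80% was the power actually used. The conclusion rests on 1:1 allocation, 63 analysed per arm, SD 20, independent participants and no variance reduction from baseline. Relaxing sidedness and attrition together reaches at most 0.905. Only an added assumption, such as a baseline-endpoint correlation of at least about 0.63, would bring power to 95%. Any clustering in the iPE groups would lower it.

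**What to change.** Keep N = 140 and correct the paragraph in Sample size {14}:

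- State about 80% power, two-sided alpha 0.05, for d = 0.5 with 63 analysed per arm. Equivalently, state 95% power for d of about 0.65 (about 13 points).
- If 95% was meant to rest on covariance adjustment, say so and give the assumed baseline-endpoint correlation with its basis.
- Name the sidedness of alpha.
- State the allowance made for shared iPE group sessions, with the assumed group size and ICC, or say that none was made.
- Reword the Discussion's power claim to match.

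The cost is one paragraph and one sentence, plus the same correction in any OSF or registry entry that repeats the figure (those records were not available to check). No additional patients are needed and trial conduct does not change. The stated power simply becomes less favourable.

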**Table Tabb:** 

*n*	Mean (reject)
100	0.759
120	0.820
140	0.878
160	0.925

### Recruitment {15}

The study will recruit participants from a psychiatric outpatient clinic in Stockholm. All clinical personnel at the recruitment site will have access to an information sheet of the study, which they can present and discuss with patients. If this will not be enough to recruit participants, self-referrals will be made available through a dedicated website, and advertisements will be placed on social media with information about the study.

### Assignment of interventions: allocation

#### Sequence generation {16a}

After the baseline assessment, participants will be randomly assigned in a consecutive manner, using a 1:1 ratio for the randomization process using block randomization. Participants will be stratified according to trauma type (exposure in childhood or as an adult) and gender. The Karolinska Trial Alliance has programmed the randomization sequence in a digital system. The system generates a unique allocation certificate with participant ID, allocation, personnel ID, and time stamp.

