### Outcomes {12}

Table 3 presents the flow of the recruitment and treatment process and lists clinician-rated and self-rated assessments at the different time points.

**Table 3 Tab3:** The flow of the recruitment and treatment process

	Enrollment	Allocation	Baseline	Week 1–5	Week 6–15	Posttreatment	1-month follow-up (primary end-point)	6-month follow-up	12-month follow-up

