**Self-rated instruments**									
PCL-5^a^			X	X	X	X	X	X	X
ITQ^a^			X	X	X	X	X	X	X
PHQ-9^b^			X		X	X	X	X	X
EQ-5D^b^			X		X	X	X	X	X
AQoL-6D^b^			X		X	X	X	X	X
TIC-P^b^			X		X	X	X	X	X
NEQ^b^					X	X	X	X	X
CEQ^c^				X					
WAI-SR^d^				X					
Treatment preference	X						X		
SUD-ratings^e^				X	X				

*Abbreviations*: *AQoL-6D* Assessing Quality of Life 6 Dimensions, *CAPS-5* Clinician-Administered PTSD Scale for DSM-5, *CEQ* Credibility/Expectancy Questionnaire, *ITQ* The International Trauma Questionnaire, *MINI* Mini International Neuropsychiatric Interview, *NEQ* Negative Effects Questionnaire, *SUD* Subjective Units of Distress Scale, *TIC-P* Treatment Inventory of Costs in Psychiatric Patients, *PHQ-9* Patient Health Questionnaire, *WAI-SR* Working Alliance Inventory–Short Form Revised

^a^PCL-5 and ITQ are administered daily during the intensive phase of treatment in the I-PE group

^b^PHQ-9, EQ-5D, AqoL-6D, TIC-P, and NEQ are administered immediately after treatment completion, w5 in the I-PE arm and w15 in the weekly delivered PE arm

^c^CEQ is administered after the first individual session in each treatment format

^d^WAI-SR is administered at the third individual session in each treatment format

^e^SUD-ratings are collected each individual treatment session

The primary outcome measure is the gold-standard clinical interview CAPS-5 that assesses PTSD symptom severity and past month diagnosis of PTSD [11] administered at enrollment, 1 month after treatment completion (primary endpoint), and at 6- and 12-month follow-ups. The CAPS-5 total severity score has high internal consistency (Cronbach’s *α* = 0.88) and interrater reliability (intraclass correlation coefficient = 0.91) and good test–retest reliability (intraclass correlation coefficient = 0.78) [11]. In this study, treatment response will be deemed successful if there is a minimum improvement of 10 points on the CAPS-5 scale between baseline and the participant’s last recorded measurement within the baseline to 12-month follow-up period. Remission will be defined as the absence of a PTSD diagnosis and/or a CAPS-5 total symptom severity score below 24, following the criteria set by Blevins et al. [12]. To be categorized as having achieved recovery, participants must maintain their remission status through the subsequent follow-up assessment.

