Secondary self-rated outcome measures are the Post-traumatic Stress Disorder Checklist for DSM-5 (PCL-5; [12]) and the International Trauma Questionnaire (ITQ; [13, 14]). These instruments are utilized to capture self-rated symptoms of PTSD and complex PTSD. Treatment response on the PCL-5 will be defined as a reduction of 10 points or more from the baseline score. Remission will be determined by a score below 30 on the PCL-5, as identified in the Swedish version of the scale by Bondjers [15], which is indicative of probable PTSD. To be classified as having achieved recovery, participants must maintain their remission status through the subsequent follow-up assessment.

Additionally, the level of depressive symptoms will be assessed using the Patient Health Questionnaire (PHQ-9; [16, 17]), and quality of life will be assessed using the EQ-5D [18].

The Assessing Quality of Life 6 Dimensions (AQoL-6D; [19]) will be administered to calculate quality-adjusted life-years for cost-utility analysis. The Treatment Inventory of Costs in Psychiatric Patients will be used to collect information on the use of medical resources, medication, social care, absenteeism, and presenteeism (TIC-P; [20]).

The Negative Effects Questionnaire (NEQ; [21]) will be used to capture potential adverse events immediately after treatment completion and the upcoming assessment points. An open-ended question asking for the occurrence of any adverse events will also be administered at each treatment session.

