### Assignment of interventions: blinding

#### Who will be blinded {17a}

The therapists and the participants in the trial cannot be blinded to treatment allocation due to the complex nature of the treatment, but group allocation will be masked to the assessors up to completion of the 12-month follow-up. Participants will receive explicit instructions not to discuss their treatment allocation with the assessor. If a participant still unintentionally discloses their treatment allocation, another blind assessor will reassess the diagnosis and symptom severity using recordings of the CAPS-5 interviews. The participant will also be assigned another assessor at subsequent follow-ups. After each assessment, the assessors will be asked to guess the participants’ allocation, and answers will be compared to chance at the end of the study to measure blinding integrity. Data managers, primary outcome assessors and trial statisticians will be blinded to group allocation until the final data analyses are completed.

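### Table 3 puts the self-rated baseline after allocation although {16a} randomises after baseline, so unblinded participants could give these scores knowing their arm

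*Protocol article*

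**What the plan says.** Sequence generation {16a} gives the order in words: "After the baseline assessment, participants will be randomly assigned in a consecutive manner". It does not say what the baseline assessment contains.

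Table 3 gives the order in columns, starting "Enrollment Allocation Baseline Week 1–5". Allocation is marked in the second column. The six self-rated instruments that have a baseline (PCL-5, ITQ, PHQ-9, EQ-5D, AQoL-6D, TIC-P) have their first mark in the third.

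The CAPS-5 is different. The text of Outcomes {12} has it "administered at enrollment, 1 month after treatment completion (primary endpoint), and at 6- and 12-month follow-ups", and Table 3 agrees, so it precedes allocation in both places.

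On masking, {17a} says: "The therapists and the participants in the trial cannot be blinded to treatment allocation". On the use of the self-rated baseline, Outcomes {12} says: "Treatment response on the PCL-5 will be defined as a reduction of 10 points or more from the baseline score".

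**The concern.** A baseline score is a fair reference for change because it cannot depend on the arm. A self-rating loses that protection once the person knows the arm. Here the two arms differ visibly in format, participants cannot be masked, and the plan itself records which format they prefer. Relief or disappointment at the allocation could move a symptom or quality-of-life rating made shortly afterwards.

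The quantities at stake are those built on a self-rated starting score:

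- PCL-5 response, which is counted from baseline;
- change in PHQ-9 and EQ-5D;
- the AQoL-6D starting value for the cost-utility analysis;
- any moderator in {20b} taken from a self-rating. Complex PTSD severity is the clearest case, because the plan captures it only by self-report;
- early recovery, which counts towards treatment completion, if its 10-point PCL-5 fall is measured from baseline. The text does not name the reference score.

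Baseline adjustment would not cleanly repair this, because a covariate measured after allocation may itself have been changed by allocation.

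**Working it through.** No arithmetic applies. The check sets the column positions in Table 3 against the text.

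| Item | First mark in Table 3 | Relative to Allocation (column 2) |
|---|---|---|
| CAPS-5, MINI, treatment preference | Enrollment (column 1) | before |
| PCL-5, ITQ, PHQ-9, EQ-5D, AQoL-6D, TIC-P | Baseline (column 3) | after |
| CEQ, WAI-SR, SUD ratings | Week 1–5 (column 4) | after, as expected for measures taken during treatment |
| NEQ | Week 6–15 (column 5) | after; it has no baseline |

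1. **Is the order an artefact of a broken table?** Unlikely. The CAPS-5, MINI and preference marks fall in column 1 of the same table, and the CAPS-5 position matches the text.

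2. **Does another part of the article settle it?** No. The footnotes to Table 3 deal with daily administration, the end-of-treatment measures and the session-based measures, not with the order of baseline and allocation. Participant timeline {13} describes the work before inclusion: "Prospectively eligible applicants will undergo a thorough assessment of eligibility using the MINI, CAPS-5, and a structured suicide risk evaluation assessment". No self-rated scale is named there. Data collection {18a} mentions baseline assessments without placing them before or after randomisation.

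3. **Can {16a} and Table 3 both be followed?** Only on a narrow reading. Outcomes {12} measures CAPS-5 response from baseline, yet the CAPS-5 has no mark in the Baseline column, so the article itself uses the word baseline for the enrolment interview. If {16a} uses it the same way, both statements hold, and every self-rated baseline then follows allocation. If {16a} means all baseline measures, Table 3 is in the wrong order.

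4. **What follows under each reading?**
   - {16a} covers the self-ratings and practice follows it: the table needs correcting and no data are harmed.
   - Practice follows Table 3, or {16a} means the interview only: all six self-rated baselines come after allocation, and they are exposed if the allocation has also been disclosed by then.

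5. **Which outcomes are clear of the problem?** The CAPS-5 outcomes are, because the starting interview precedes allocation. PCL-5 remission, a score below 30, uses no baseline value and is also clear.

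**The case against.** The strongest reply is that Table 3 is a loose schematic and that {16a}, the only sentence giving the order in words, states the accepted one. The table is loose elsewhere. Its footnote puts the PHQ-9, EQ-5D, AQoL-6D, TIC-P and NEQ at week 5 in the intensive arm, yet those rows have no mark under Week 1–5 and carry one under Week 6–15. A misplaced column is therefore a credible explanation. The article also does not say when participants are told their arm. Both points stand, and they limit the finding to a risk. They do not remove it, because the schedule is what staff and readers work from and nothing in the article corrects it.

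Four stronger readings are tempting, and the documents do not support them.

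- *The two statements are flatly incompatible, or self-rated baselines were in fact taken after allocation.* The narrow reading of {16a} reconciles the statements, and no record of practice is given.
- *The bias can be sized.* One might say that a shift of k points in one arm's baseline PCL-5 moves the between-arm contrast in change by k points. That holds for unadjusted change scores, but the analysis model is in a separate file that was not available here. No shift is documented, so any value would be an assumption.
- *Participants who refuse their arm would lack a self-rated baseline, more often in one arm.* Nothing shows this, and inclusion requires being able to attend either format.
- *Existing time stamps would settle the matter.* The only time stamp described is on the allocation certificate. The article does not say whether the BASS questionnaires carry one.

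**Conclusion.** The inconsistency is real and should be corrected. Section {16a} and Table 3 give different orders for the self-rated measures unless {16a} means only the enrolment interview, and that reading is the one that puts the self-ratings after allocation.

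The reach is six self-rated instruments and the secondary, health-economic and moderator analyses that use their starting scores. The primary outcome is not affected. The documents support no figure for the size or direction of any bias. The conclusion that bias is possible rests on two conditions that the article leaves open: that the self-ratings are collected after allocation, and that participants know their arm by then. The matter is moderate in weight: more than clerical, because following the schedule as printed would weaken these reference scores, but it does not threaten the main result.

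**What to change.** 1. Reorder Table 3 to Enrollment, Baseline, Allocation.
2. State in {16a} that the CAPS-5 and all baseline self-ratings (PCL-5, ITQ, PHQ-9, EQ-5D, AQoL-6D, TIC-P) are completed before the allocation is generated and disclosed.
3. For participants already randomised (inclusion began in September 2023), check from whatever records exist whether any self-rated baseline was given after allocation. If none was, say so; nothing further is needed.
4. If some were, report how many in each arm, and add a sensitivity analysis of the self-rated outcomes that does not rely on those baselines. For example, compare follow-up scores without subtracting or adjusting for the affected values, and repeat PCL-5 response without the affected participants, noting that this exclusion gives up part of the randomised comparison.

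The first two steps change a table and add a sentence. The third is a records check. The fourth arises only if the third finds cases. No visits are added. The cost in practice is that allocation waits until the questionnaires are finished.
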